### **f. Sample Size**

One self-management study (Walters et al., 2013) examined the effects of a telephone self-management program in COPD patients and used both the PIH scale and SGRQ. The effect size of the change over a 6m between the control and the intervention group was 0.42 for the PIH and -0.27 for the SQHQ. Assuming an  $\alpha=0.05$ , and correlation between repeated measures of 0.85, a total sample of 82 for a comparison between one of the intervention groups and the standard care group at baseline and 6m (41 patients per group) will produce power of 0.97 for PHI and 0.71 for the SGHQ. It is not clear whether we'd see any changes at 3m, but we are confident that we'd detect some effects at 6m.

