#### **c. Recruitment**

Recruitment will be on-going until 123 patients have been recruited for the intervention phase (see sample size justification in Section 6.b). Patients will be approached by the clinical staff (respirologist or respiratory therapist-RT) who will introduce the technology to them and provide them with brief information about the trial with a brochure (Appendix 19) and request permission to pass the patient's information to the clinical project specialist at MSH. At this time the consent

form will also be given to give the patients enough time to consider participation. The clinical project specialist will later call the participants to further inquire about their interest in participating and to provide further details about the project. At this time they will also confirm the patient has a copy of the consent form and if they don't have the clinical project specialist will email it to the patient. The patients who are still interested in the project will be scheduled for their baseline evaluation, at which time informed consent will be signed (Appendix 1) and the Cloud DX kit will be provided to them. Patients can split that session into two, if they feel it is too much for one visit. There will also be a recruitment video that will be uploaded on YouTube. The clinical project specialist will email the link with the brochure to interested patients. The clinical project specialist will also be showing the video on a tablet to patients in the Outpatient COPD Exercise Rehabilitation Program. The Inpatient RT will show the video on a tablet to patients with COPD prior to their discharge from hospitalization.

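### The stated power (0.97 PIH, 0.71 SGRQ) matches a mean difference entered as Cohen's f; for a two-sided test of the 6-month change it is 0.47 to 0.95 and 0.23 to 0.63, depending on an SD the protocol does not state

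*Protocol*

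**What the plan says.** The only sample-size justification is the paragraph in Protocol section 4.f. It draws on one earlier trial of a telephone self-management programme: "The effect size of the change over a 6m between the control and the intervention group was 0.42 for the PIH and -0.27" for the SGRQ. It then assumes alpha 0.05, a "correlation between repeated measures of 0.85", and two measurements in two groups: "a total sample of 82 for a comparison between one of the intervention groups and the standard care group at baseline and 6m (41 patients" in each). From these it concludes that the sample "will produce power of 0.97 for PHI and 0.71 for the SGHQ". It closes by expressing confidence that some effects will be detected at 6 months.

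The paragraph does not name the test, say whether alpha is one- or two-sided, or say which SD scales the effect sizes. The preceding section on statistical analysis plans a between-group repeated-measures ANOVA over baseline, 3 and 6 months. Section 4.c adds: "Recruitment will be on-going until 123 patients have been recruited for the intervention phase".

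**The concern.** The cited effects are signed and describe a difference in change between two groups. They are therefore standardised mean differences (d). Cohen's f, the effect measure in ANOVA power routines, cannot be negative, and for two equal groups it equals d/2. Entering d where f is expected doubles the effect.

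There is a second mismatch. The between-groups term of a repeated-measures ANOVA compares means averaged over all visits, including baseline, where randomisation leads us to expect no difference. It does not test the difference in change, which is the effect the paragraph cites.

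This matters because readers will use the paragraph to judge how informative a null result is. If power is well below what is stated, a non-significant PIH or SGRQ comparison could be misread as evidence of no benefit.

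**Working it through.** **Inputs, all from Protocol section 4.f.** Effects 0.42 and 0.27 in absolute value; alpha 0.05; correlation r = 0.85; N = 82 (41 per group); m = 2 visits.

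**Step 1: reproduce the stated figures.** For the between-groups effect in a repeated-measures ANOVA, lambda = f² x N x m / (1 + (m - 1) x r), with 1 and N - 2 = 80 degrees of freedom.

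- PIH, f = 0.42: lambda = 0.1764 x 164 / 1.85 = 15.64; power 0.974 (stated 0.97).
- SGRQ, f = 0.27: lambda = 0.0729 x 164 / 1.85 = 6.46; power 0.709 (stated 0.71).

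Both agree to two decimals under one setting. Three alternatives do not match:

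- the same test with three visits: 0.977 and 0.721;
- the group-by-time term with the effects entered as f: above 0.99 for both;
- a two-sample t-test with d = 0.42 and 0.27: 0.468 and 0.227.

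**Step 2: the same test with f = d/2.**

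- PIH, f = 0.21: lambda = 15.64 / 4 = 3.91; power 0.497.
- SGRQ, f = 0.135: lambda = 6.46 / 4 = 1.62; power 0.241.

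Even this assumes that the full difference is present at both visits, so it is still not a test of change.

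**Step 3: a two-sided 0.05 test of the 6-month change, 41 per arm.** Noncentral t with noncentrality d x sqrt(n/2). The answer depends on which SD scales 0.42 and 0.27.

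- *SD of change.* Use d directly: 0.42 x sqrt(20.5) = 1.90 and 0.27 x sqrt(20.5) = 1.22.
- *Raw-score SD, change score.* SD of change = sqrt(2 x (1 - 0.85)) = 0.548 raw SD, so d = 0.42 / 0.548 = 0.767 and 0.27 / 0.548 = 0.493. The group-by-time term over baseline and 6 months is the same test and gives the same power.
- *Raw-score SD, baseline-adjusted.* Residual SD = sqrt(1 - 0.85²) = 0.527, so d = 0.797 and 0.513.

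| Scaling and test | PIH | SGRQ |
|---|---|---|
| Stated in the protocol | 0.97 | 0.71 |
| SD of change | 0.47 | 0.23 |
| Raw-score SD, change score | 0.93 | 0.60 |
| Raw-score SD, baseline-adjusted | 0.95 | 0.63 |

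**Step 4: dependence on r.** The protocol gives no source for 0.85, and the raw-SD rows depend on it. Change-score power is 0.68 and 0.35 at r = 0.70, 0.84 and 0.48 at r = 0.80, and 0.99 and 0.77 at r = 0.90.

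**Step 5: loss to follow-up.** The recruitment target of 123 equals 3 x 41, so power is stated for complete follow-up. The protocol gives no loss figure. Taking 15% as an assumption, 41 x 0.85 = 34.85, or about 35 per arm:

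- SD of change: 0.41 (PIH) and 0.20 (SGRQ).
- Raw-score SD, change score, r = 0.85: 0.89 and 0.53.

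**The case against.** The strongest counter-argument is that the cause is inferred. No test or sidedness is given, and another route comes close: a one-sided 0.05 change-score test with raw-SD effects gives 0.964 and 0.715. That stands as a reason to say that the figures match the Cohen's f route, not that they are proven to come from it. The one-sided route is nevertheless the weaker explanation. Its 0.964 does not round to 0.97, its 0.715 lies on the border between 0.71 and 0.72, the paragraph mentions no one-sided test, and the planned ANOVA F test has no direction.

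The second argument is that the primary comparison may still be well powered. If the effects are in raw-score SDs and r = 0.85 holds, PIH power falls by only 2 to 4 points and stays well above 0.80. That also stands. The protocol supplies a correlation, which a test of change needs only under raw-SD scaling, although a repeated-measures formula would need it too. SGRQ is a secondary outcome, and the protocol's own figure for it is already below 0.80.

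A reader might therefore be tempted by two stronger conclusions. One is that the true power is 0.47 and 0.23, making the primary comparison roughly a coin-flip. That holds only if the unstated SD is the SD of change, which the paragraph's wording neither confirms nor excludes. The other is that the trial is too small and must be enlarged. The documents do not establish that, because the favourable reading remains open.

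**Conclusion.** The power sentence is wrong as written. At the protocol's own correlation of 0.85 and 41 per arm, none of the two-sided tests of the 6-month change worked through here reaches 0.97 for PIH or 0.71 for SGRQ. The shortfall for PIH ranges from 2 points (0.95, raw-score SD, baseline-adjusted) to 50 points (0.47, SD of change). For SGRQ it ranges from 8 points (0.63) to 48 points (0.23).

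The arithmetic match to d entered as f is exact to two decimals, but the route remains an inference. Where the truth lies in the range depends on the scaling SD, which the protocol does not state, and on an unsourced r. The 0.93 and 0.60 of the unadjusted change score should not be read as a ceiling, since baseline adjustment gives 0.95 and 0.63. The lack of any allowance for loss lowers each figure further; how far depends on an assumed completer number.

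**What to change.** Rewrite the paragraph in Protocol section 4.f:

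- Name the test of the 6-month change that the power refers to, and say whether it is one- or two-sided. The planned ANOVA need not be replaced, because its group-by-time contrast of baseline with 6 months is such a test.
- State which SD scales 0.42 and 0.27, checked against the cited trial.
- Replace 0.97 and 0.71 with the matching pair for 41 per arm: 0.47 and 0.23 (SD of change), 0.93 and 0.60 (raw-score SD, change score), or 0.95 and 0.63 (raw-score SD, baseline-adjusted).
- Give the corresponding power for an assumed number of completers, with the loss assumption stated.
- Remove the closing statement of confidence about detecting effects at 6 months.

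Keep N = 123. The cost is one reworded paragraph and less favourable stated power; no extra patients are needed.

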#### g. Data Collection

All assessment data will be collected by the clinical project specialist at MSH and entered into a de-identified database that will be then sent to the research coordinator at Women's College Hospital. The clinical project specialist will also assign a Cloud DX ID that will be distinct from the REDCap ID. REDCap IDs will be consecutive, while Cloud DX IDs will be random, so that they cannot be easily linked to each other. All data will be entered into REDCap by the clinical project specialist.

Data collected through the chart review will be collected and tracked using the Health Care Utilization Chart Review Tool (Appendix 22 - COPD Cloud DX Health Care Utilization Chart Review Tool).

#### h. Data Management

All data will be stored on password protected computers accessible only by members of the research team in locked rooms at Women's College Hospital. All data will be gathered from original sources, including the Cloud DX data management system, and directly from patient surveys or interviews and transferred to Women's College Hospital for storage through REDCap. The participants will be identified only through a participant ID number. The information will be encrypted and will be accessed by the study team through a secure VPN. A data sharing agreement which will detail how data will be transferred and stored between Women's College Hospital, Markham-Stouffville Hospital and Cloud DX is currently being drafted and will be signed by all parties in the study prior to data transfer.

### **Study Significance**

The use of technology has the potential to provide clinical marker feedback to the patient and the clinical care provider (RM group), resulting in better disease control and better self-management skills and quality of life. Both programs have the potential to result in fewer face-to-face visits (outpatient and inpatient admissions), but the RM group may be more effective in that regard due to its ability to directly communicate with patients. The goal is to empower patients and improve their self-management skills leading to faster resolution of their health concerns resulting in fewer complications that may lead to outpatient and inpatient visits. This will increase institutional capacity to offer extended healthcare services to more patients.

### **Risks**

There is a risk that participants may feel uncomfortable with some items on some of the scales. If participants feel upset at any time during their participation in the study, they will be given the option to stop. In addition, there is a risk that some patients may feel more anxious about their disease once they know what their readings are or if their readings fall below threshold. We will advise patients to contact their health care provider or go to the emergency if they feel unwell or get anxious about their readings.

Participants who have extremely busy schedules and/or are trying to balance multiple personal, health and work demands may feel stress at the thought of taking time to participate in the study. At recruitment we will stress that participation is voluntary.

### **Benefits**

The findings of the study may contribute to a greater understanding of the effects of self and remote-monitoring in patients' ability to manage their disease. Patients will also receive the Cloud DX kit system for free and will keep it after completion of the study.

## **Qualitative Realist Evaluation Protocol**

### **Background**

In order to understand the contextual influences and practical processes of the Cloud DX platform implemented in MSH, we will use a qualitative process evaluation informed by realist methodology (Pawson, 2013). Realist Evaluation is a methodology used to “unpack the black box of implementation” (Marchal, van Belle, van Olmen, Hoérée, & Kegels, 2012), examining the actual actions required by those involved in implementation to ensure the Cloud DX platform is taken up and used by the clients and health care providers involved. This methodology enables a rigorous assessment of the contextual influences and strategies by which the application is adopted or rejected, enabling researchers to understand how and why the implementation succeeds or fails. Although we do not have resources to complete a full realist evaluation, our process evaluation incorporates principles of realist evaluation in order to provide insight into who benefits from the use of Cloud DX in what circumstances, and how. In order to best understand the mechanisms by which the technology was implemented, we will use a framework called the “Tool+Team+Routine” framework. This approach directs researchers’ attention to the stakeholder who make up the team of people using the technology (including patients), the technology itself, and the new routines that need to be developed in order to successfully use the technology in everyday life. Interview questions will focus specifically on these elements in order to better illuminate the mechanisms involved.

### **Objectives**

The objective of the qualitative realist evaluation component of this study is to (a) understand how the Cloud DX platform is implemented in practice, (b) explore participants and members of the care team’s perspectives of the usability and acceptability of the Cloud DX platform, and (c) examine the key issues associated with scaling of the Cloud DX platform in other settings across Ontario.

### **Methods**

The qualitative process evaluation will occur alongside the clinical trial described above, and will include semi-structured interviews with end users involved in the implementation process. Qualitative interviews will be conducted with participants and/or their caregivers, their healthcare providers, and hospital administrators/managers. . Ten participants/caregivers, four healthcare providers, and three hospital administrators/managers will be recruited.

Qualitative interviews will include questions about (a) participants’ experiences of learning about and using the technology; (b) changes to healthcare provider workflow required to effectively use the technology; (c) organizational changes required to support the technology; and (d) health system barriers and facilitators to effective implementation and evaluation (See Appendix 11A-C for Interview Guide). The interview guide includes specific questions related to the feasibility of the evaluations taking place, offering participants the opportunity to provide direct input into the implementation process. These qualitative interviews will be audio recorded and transcribed verbatim, and analyzed using thematic analysis strategies (Braun & Clarke, 2006; Pawson, 2013) by the investigator team to identify key themes related to the implementation and evaluation of Cloud DX in actual contexts of health care delivery in Ontario.

### **Recruitment**

#### **Patients**

Potential participants will be identified prospectively by the clinical project specialist at MSH, based on whether they expressed interest during their consent process for the quantitative study. Individuals who express interest in the qualitative phase of the study will be directed to place a checkmark in the appropriate checkbox on the quantitative study consent form and their interest will be recorded in REDCap. The clinical project specialist at MSH will forward the names of the participants who are selected for the qualitative phase by the research coordinator at WCH, who in turn will contact the patients directly to follow-up, further explain the qualitative component of the study, provide the consent form, and schedule the interviews. Five patients from the RM and five from the SM group (and/or their caregiver if they were involved in taking measures) will be included in this stage. Healthcare providers involved in the care of participants and hospital administrators/managers will also be approached for participation in the qualitative portion of the study and interviewed upon study completion. These would include up to six healthcare providers involved in the care of patients who have participated in the quantitative part of the study and would include respirologists, RTs, and family doctors of the participants, and up to five hospital administrators/managers. These interviews will last no more than 60min each.

### **Data Analysis**

Qualitative interviews will be immediately transcribed into word documents and prepared for qualitative analysis. The findings of the qualitative data will be used to develop statements of the relationships between (a) key contextual factors, (b) the mechanisms by which they effect the implementation of the Cloud DX platform, and (c) the impact on the outcomes of the intervention themselves (in Realist Evaluation these statements are referred to as “Context-Mechanism-Outcome Configurations”)(Pawson, 2013). These statements will be used to revise a in order to accurately reflect the key contextual influences and practices that constitute the implementation process in actual health care settings in Ontario.

### **Privacy and Confidentiality**

All transcripts will be de-identified and data analysis will be aggregate in nature. Data stored electronically will be encrypted and password protected. Data will only be accessible to the investigators and hired research personnel who have received training in ethical and privacy principles.

Consent forms of study participants will be stored separately from the data files (transcripts and analytical worksheets). Only the Principal Investigator will have access to the consent forms, which will be kept in a locked cabinet for a period of 10 years. Once the dialogue from the interview audiotape(s) has been transcribed, the audiotape(s) will be destroyed. Password protected electronic copies of the transcribed audiotapes will be disseminated via email to the Investigative Team with the understanding that they will be destroyed after analysis. The hard copies of data (transcripts and analytical worksheets/notes) and informed consent forms will be shredded 10 years after study completion.

### **Risks**

There are no known harms associated with participation in this qualitative portion of the study.

There is a risk that participants may feel uncomfortable with items of discussion, or with being tape recorded. However, participants may withdraw from the study at any time or refuse to participate in any conversation that they find uncomfortable or embarrassing. If participants feel

upset at any time during their participation in the study, they will be given the option to stop. Participants will be given the option to have their de-identified data removed if they wish to.

Participants who have extremely busy schedules and/or are trying to balance multiple personal, health and work demands may feel stress at the thought of taking time to participate in an interview.

#### Benefits

The findings of the study may contribute to a greater understanding of the effects of self and remote-monitoring in patients' ability to manage their disease.

#### Conflicts of Interest

No known conflicts of interest.

